###### DATA ANALYSIS / SUBJECT SELECTION

**Statistical Considerations**:

**Sample size and power calculations**:

This study is a pilot/ feasibility study. The primary hypothesis of this study is to compare changes in PKC activity due to the transition from a traditional Asian diet to a typical American diet in two different ethnic groups, Asian and Caucasian. The interest is the mean percent change in marker levels between the two ethnic groups, which would be the values at timepoint 3 (after exposure to American diet) minus the values at timepoint 2, divided by the measure at time point 2 times 100. This would give the percent change that could be accounted for by exposure to the different diets in each ethnic group. For this comparison, the power for comparing the net change between the two ethnic groups of 20 individuals who will change from a traditional Asian diet to an American diet was calculated. Additionally, two control groups (one of each ethnicity) will remain on the traditional Asian diet as a control for potential outside effects on the primary hypothesis, the power calculations for comparing the control group to the active group can also be found below.

A total of 25 individuals of each ethnic group will be randomized into either the traditional Asian diet group (n=5) for each period or into the traditional diet and then the American diet (n = 20). The total number of participants is limited by cost. It is our hope that the 5-person control arms makes it possible to assess whether a factor outside of diet contributed to any differences observed. These control groups of ten will only be used for a subset analysis to get an idea of possible environmental effects on the outcome of interest, change in PKC activity. An appropriate two-sample test will be used for this determination, with the alpha and power given in the proceeding paragraph.

The power for the examination of percent change in PKC activity, the primary hypothesis, was calculated using STATA 7.0 (College Station, Texas 2001). An assumption of a one-sided test with an alpha of 0.05 was made. Mean PKC measurements were estimated at 78.1*[[6]](#endnote-7)* ±5 (there is no expected ethnic variation in PKC activity levels). Calculations are based on change exhibited by cardiac cells with exposure to increased lipids. In previous trials a 50% change has been observed in PKC activity in the cytosol of cardiac cells.

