Table 1. Power calculations for PKC activity percent change to detect a difference between Caucasian and Asian American groups when exposed to the American diet.

| **Size of Group 1** | **Size of Group 2** | **Percent change** | **PKC estimate** | **PKC Std dev (+)** | **Power** |
| --- | --- | --- | --- | --- | --- |
| 25 | 25 | 10 | 85.91 | 5.5 | 0.999 |
| 25 | 25 | 5 | 82.005 | 5.25 | 0.8527 |

This summary table of power to detect a significant difference suggests that a study using this approach would have adequate power to detect a difference between the two groups in PKC activity. We do not expect to see a difference less than 5%.

Table 2.  Power calculations for PKC activity change with change in diet based on a comparison to detect a difference between the control group and those exposed to the American diet. The baseline PKC activity value used in this calculation is 78.1 5.

| **Size of Group 1** | **Size of Group 2** | **Percent change** | **Comparison values** | **Power** |
| --- | --- | --- | --- | --- |
| 10 | 25 | 10 | 85.91 5.5 | 0.969 |
| 10 | 25 | 5 | 82.005 5.25 | 0.875 |

This demonstrates that we have adequate power to detect as low as a 5% change between the two groups. This exceeds our needs as estimated change is approximately 50%.

In addition to the primary endpoint of change in PKC levels, changes in Flow Mediated Dilation (FMD) and CRP are of interest. These differences will be examined by two-sample tests, either two-sample t or Wilcoxon sign rank. The power curves based on current literature for changes in FMD can be found below, based on a one-sided hypothesis using an alpha of 0.05, for the detectable difference of percent change between ethnic groups. The power to detect a difference in percent change for CRP measures was also examined. Our estimates indicate that there is insufficient power (~50%) to detect a difference as large as 25 between the two percent change measures. This was calculated assuming a one-sided test with an alpha of 0.05.

 Additionally, we present the power curve for the detection of difference in percent change in Flow Mediated Dilation.

Figure 1. Power curve for percent difference in FMD between Caucasians and Asians (the x-axis represents difference between the two measures) [[7]](#endnote-8),[[8]](#endnote-9) ,[[9]](#endnote-10),[[10]](#endnote-11)

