**Data Analysis:**

Our primary a priori hypothesis is to detect if there is a difference in PKC activity change between Caucasians and Asians with exposure to American diets, which will be done through a two-sample test (either t-test or Wilcoxon signed-rank sum, depending on distribution). A secondary hypothesis is to examine the difference in change of Flow Mediated Dilation before and after exposure to the American diets between the two ethnic groups, which will also be examined through a two-sample test. These will be examined with an alpha set at 0.05. Additionally, we expect to do several exploratory analyses, including anthropometrics, lipids, fibrinogen, IL-6, TNF-alpha, E-selectin, Isoprostane, Fox II, leptin, adiponectin, and ghrelin. We will use Scheffé’s procedure for linear contrasts, as the comparison of means is a special case of this to help correct for multiple comparisons. However, correction for multiple comparisons will be applied for all exploratory hypotheses.

Multiple potential confounding variables will be controlled for by including limitations on age, family history of diabetes, limited range of BMI (estimated body fat content), and physical activity. We will also take a diet history and exclude those with medical illnesses. These steps will not exclude all bias but should limit it in this study. The potential role of effect-modifiers will also be considered in the interpretation of the data. A preliminary stratified examination will be done to determine if there is a significant difference between exposed and unexposed groups of the same ethnicity. Baseline and post intervention measures permits change from baseline analysis. If change from baseline differs between groups, we are interested in designing future studies to identify the factors that mediate the differences in response between ethnic groups.

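### Table 2's power of 0.875 for a 5% control-versus-switch difference does not follow from its own inputs (0.63 to 0.66), and the claim of adequate power for 5% is unsupported

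*Protocol*

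**What the plan says.** The power section rests on one set of assumptions. On the test: "An assumption of a one-sided test with an alpha of 0.05 was made". For the control comparison it refers to the same basis: "An appropriate two-sample test will be used for this determination, with the alpha and power given in the proceeding paragraph". The baseline is given before Table 2: "The baseline PKC activity value used in this calculation is 78.1", with an SD of 5.

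Table 1 of that section (Caucasian v Asian) has this row for a 5% change: "25 | 25 | 5 | 82.005 | 5.25 | 0.8527". Table 2 (control v American diet) uses the same comparison mean and SD for 5%, with group sizes 10 and 25, and states power 0.875. Its 10% row states 0.969. The conclusion is "This demonstrates that we have adequate power to detect as low as a 5% change between the two groups".

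The group sizes are not consistent across the protocol. The Study Design text assigns 10 of 35 per ethnic group to control and 25 to the switch. The table in the same section, and the text of the power section, have 5 and 20 of 25. The power section speaks of the smaller arms: "It is our hope that the 5-person control arms makes it possible to assess whether a factor outside of diet contributed". It then also mentions control groups of ten, which can be read as the two arms of five combined. The Data Analysis section describes a stratified look "to determine if there is a significant difference between exposed and unexposed groups of the same ethnicity".

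**The concern.** Tables 1 and 2 disagree without any calculation. For the same difference, SDs and alpha, cutting one group from 25 to 10 cannot raise power from 0.8527 to 0.875. At least one of the two figures must be wrong.

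The control arms are the only concurrent check on whether a PKC change after the switch is due to diet. An outside factor would act on controls and switchers alike and so would leave little difference between them. It is a clear difference between the arms that would support attribution to diet. If power is overstated, a non-significant difference invites over-reading. With a claimed power of 0.875 it could be taken to mean that diet added nothing, or that outside factors explain the change, when the comparison may simply have been too small.

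**Working it through.** **Inputs.** Control mean 78.1, SD 5 (power section text and the line above Table 2). Comparison mean 82.005, SD 5.25 for 5%; 85.91, SD 5.5 for 10% (Tables 1 and 2, reading the paired values in Table 2 as mean and SD, as Table 1 labels them). One-sided alpha 0.05, critical value 1.645. Differences: 82.005 − 78.1 = 3.905 and 85.91 − 78.1 = 7.81.

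**Formula.** Power = Φ(difference / √(SD₁²/n₁ + SD₂²/n₂) − 1.645).

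**Step 1: reproduce Table 1 (5%, 25 v 25).** √(25/25 + 27.5625/25) = √2.1025 = 1.450. 3.905/1.450 = 2.693; 2.693 − 1.645 = 1.048; Φ = **0.8527**. This equals the stated figure to four decimals, so this is evidently the protocol's method.

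**Step 2: the same formula for Table 2 (5%, 10 v 25).** √(25/10 + 27.5625/25) = √3.6025 = 1.898. 3.905/1.898 = 2.057; 2.057 − 1.645 = 0.413; Φ = **0.660**, against 0.875 stated.

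**Step 3: check by t-test.** The pooled t gives 0.628 and the Welch t 0.630. Swapping the SDs between groups gives 0.61 to 0.64. Two-sided versions with the stated SDs give 0.47 to 0.54. No two-sample version tried at alpha 0.05 with 10 v 25 comes near 0.875.

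**Step 4: other group sizes, one-sided 0.05.**

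| Sizes (control v switch) | 5%: normal | 5%: pooled t | 10%: normal | 10%: pooled t |
|---|---|---|---|---|
| 10 v 25 (Table 2; Study Design text, within ethnicity) | 0.660 | 0.628 | 0.992 | 0.985 |
| 5 v 20 (power section, within ethnicity) | 0.461 | 0.425 | 0.922 | 0.876 |
| 10 v 40 (power section, both ethnic groups pooled) | 0.706 | 0.673 | 0.996 | 0.991 |

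For example, 5 v 20 at 5%: √(25/5 + 27.5625/20) = √6.378 = 2.525; 3.905/2.525 = 1.546; 1.546 − 1.645 = −0.099; Φ = 0.461. For 10 v 40 at 5%: √(2.5 + 0.6891) = 1.786; 3.905/1.786 = 2.187; Φ(0.542) = 0.706.

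**Step 5: what these figures depend on.** The endpoint is percent change, but the SD of 5 belongs to single PKC levels. The protocol gives neither an SD of percent change nor a within-subject correlation. If change scores are used and a correlation ρ between the two time points is assumed (variance multiplied by 2(1 − ρ)), power for 5% is:

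| Assumed ρ | 10 v 25 | 5 v 20 | 10 v 40 |
|---|---|---|---|
| 0.25 | 0.51 | 0.35 | 0.56 |
| 0.50 | 0.66 | 0.46 | 0.71 |
| 0.70 | 0.84 | 0.64 | 0.88 |
| 0.75 | 0.90 | 0.71 | 0.93 |

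So 0.875 at 10 v 25 would need ρ between 0.70 and 0.75, which the protocol nowhere assumes.

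**The case against.** The strongest reply is that this is a pilot whose size is set by cost, that the controls serve only a subset analysis, and that the protocol expects a change near 50%. This largely stands as to weight. At 50% the difference is 39.05; with the SD scaled as in the tables (5 × 1.5 = 7.5), 5 v 20 gives 39.05/√(25/5 + 56.25/20) = 13.97, so power is essentially 1. At 10% it is still 0.88 to 0.92. But the protocol makes a separate claim about 5% and supports it with a wrong number. It admits low power for CRP and for the gingival fluid correlation, and this comparison needs the same treatment.

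A second reply is that the Study Design text, at 35 per ethnic group, gives 20 v 50 when pooled, where 5% power is 0.88 to 0.90. That is correct arithmetic, but Table 2 prints 10 v 25. At 20 v 50 the 10% row would be about 0.9999 rather than 0.969, so this does not explain the table.

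Three stronger readings are tempting and should not be drawn:
- A reader might infer that a true 5% difference would be missed more often than found. On the stated SDs that holds at 5 v 20 only; at 10 v 25 and 10 v 40 one-sided power exceeds one half.
- A reader might infer that a non-significant result would falsely reassure about outside factors. The direction is the reverse: an outside factor acts on both arms, so the absence of a difference is not reassurance.
- A reader might count the 10% row as a second material error. It is stated at 0.969 against 0.985 to 0.992, which is small and conservative, and a two-sided Welch t gives 0.9695.

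**Conclusion.** The point holds in this form: 0.875 is wrong for Table 2's own inputs, by about 21 percentage points on the protocol's formula (0.875 − 0.660) and 25 on the t-test (0.875 − 0.628). Power for a 5% difference is below 0.80 at 10 v 25, at 5 v 20 and at pooled 10 v 40, so the adequacy sentence is unsupported under each of these.

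The figures rest on one-sided alpha 0.05 and on the SD of single PKC levels. They correct the protocol's arithmetic; they are not the power of the percent-change analysis, for which the protocol gives no variance. The group sizes also remain in conflict. 5 v 20 has the better support, but the document does not settle it.

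The consequence is limited. The error concerns a subset comparison in a pilot, adequate power for about a 10% change remains, and the primary between-ethnicity test is not affected by it. A reader might conclude that the study as a whole is underpowered because of this table; the documents do not support that.

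**What to change.** 1. Reconcile the group sizes: the Study Design text (10 and 25 of 35 per ethnic group) against its own table and the power section text (5 and 20 of 25).
2. Recompute Table 2 for the reconciled sizes, naming the test and stating whether the comparison is within ethnicity or pooled. For 5 v 20: about 0.42 to 0.46 at 5% and 0.88 to 0.92 at 10%. For 10 v 40: about 0.67 to 0.71 and 0.99 or more. If 10 v 25 is kept: 0.63 to 0.66 and 0.985 to 0.992.
3. Label the figures as conditional on the SD of single PKC levels, since no SD of percent change is available.
4. Replace the adequacy sentence with one saying that the control comparison has adequate power for about a 10% change but not for 5%.
5. Report the control-versus-switch difference with a confidence interval. State that a non-significant difference neither shows that diet had no effect nor attributes the change to outside factors.

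Once the sizes are settled, the cost is one table and two or three sentences. This correction by itself changes no procedure and not the primary analysis; the stated power simply becomes less favourable.

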**Data Analysis:**

Our primary a priori hypothesis is to detect if there is a difference in PKC activity change between Caucasians and Asians with exposure to American diets, which will be done through a two-sample test (either t-test or Wilcoxon signed-rank sum, depending on distribution). A secondary hypothesis is to examine the difference in change of Flow Mediated Dilation before and after exposure to the American diets between the two ethnic groups, which will also be examined through a two-sample test. These will be examined with an alpha set at 0.05. Additionally, we expect to do several exploratory analyses, including anthropometrics, lipids, fibrinogen, IL-6, TNF-alpha, E-selectin, Isoprostane, Fox II, leptin, adiponectin, and ghrelin. We will use Scheffé’s procedure for linear contrasts, as the comparison of means is a special case of this to help correct for multiple comparisons. However, correction for multiple comparisons will be applied for all exploratory hypotheses.

Multiple potential confounding variables will be controlled for by including limitations on age, family history of diabetes, limited range of BMI (estimated body fat content), and physical activity. We will also take a diet history and exclude those with medical illnesses. These steps will not exclude all bias but should limit it in this study. The potential role of effect-modifiers will also be considered in the interpretation of the data. A preliminary stratified examination will be done to determine if there is a significant difference between exposed and unexposed groups of the same ethnicity. Baseline and post intervention measures permits change from baseline analysis. If change from baseline differs between groups, we are interested in designing future studies to identify the factors that mediate the differences in response between ethnic groups.

Additionally, an underpowered study of the correlation between GCF and inflammatory markers will be done using linear regression. As there are limited observations, only the idea of a trend is expected from this analysis. . It is recognized that several factors may differentially contribute to dental health, and could therefore, affect the findings of this analysis. An attempt to correct for these factors was made through the exclusion criteria, which rules out people who have smoked and those with other chronic diseases, which may be related to periodontal health. The age range of the population examined is also constrained to limit possible effect modification by age.

Data analysis will start with a univariate examination of variables, primarily for the determination of whether parametric or non-parametric statistics are appropriate. Hypothesis testing, for the primary hypothesis, will be undertaken using two sample t-tests or Wilcoxon Rank Sum test for continuous variables.

Due to the preliminary nature (pilot/ feasibility) of this study and small sample size, multivariable model building will only be done on an exploratory basis and is expected to be underpowered.

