**Details of Measurements:**

1. **Anthropometric measurements**- measurements of weight, height, waist, hip ratio
2. **Dual Energy X-Ray Absorptiometry (DEXA)**- to evaluate total and regional body fat mass. This measurement will follow standard procedure for body composition measurement and will be performed on Hologic Delphi-A 70372. (Only at End of week 2 (V2), End of 11 (V3), and End of week 18(V4))
3. **Fasting Lipid Panels**- Total cholesterol, HDL, LDL, TG
4. **Hypercoaguability** markers- plasminogen activator inhibitor – 1(PAI-1)
5. **Systolic/Diastolic Blood Pressure**
6. **Insulin Sensitivity** – HOMA-IR, Fasting insulin and glucose level, hemoglobin A1c
7. **Inflammatory markers**- PKC levels in monocytes, CRP, Isoprostane, RNA, IL-6, IL-8, TNF-α, and IL1-.
8. Other **hormones** related to weight and insulin resistance: TSH (Sceening visit only), leptin, adiponectin, ghrelin.
9. **Dental** assessments and collection of GCF to be performed by Harvard School of Dental Medicine.

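### Scheffé's procedure, the only multiplicity method named for the exploratory outcomes, does not adjust across outcomes, and two or three listed markers have no stated measurement

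*Protocol*

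**What the plan says.** The Data Analysis section of the protocol sets out three tiers.

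- **Primary:** the "difference in PKC activity change between Caucasians and Asians with exposure to American diets, which will be done through a two-sample test".
- **Secondary:** the change in FMD, compared between the same two ethnic groups, also with a two-sample test. Of these two hypotheses it says "These will be examined with an alpha set at 0.05".
- **Exploratory:** several analyses, "including anthropometrics, lipids, fibrinogen, IL-6, TNF-alpha, E-selectin, Isoprostane, Fox II, leptin, adiponectin, and ghrelin". That is eleven named items in an open list.

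For multiplicity it names Scheffé's "procedure for linear contrasts, as the comparison of means is a special case of this to help correct for multiple comparisons". The next sentence opens with a contrasting word and promises that "correction for multiple comparisons will be applied for all exploratory hypotheses". It names no other method.

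Details of Measurements lists what is collected. The inflammatory markers begin "PKC levels in monocytes, CRP, Isoprostane, RNA, IL-6, IL-8" and continue with TNF-alpha and IL-1. PAI-1 is the only hypercoagulability marker. The hormones are TSH, leptin, adiponectin and ghrelin.

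**The concern.** A multiplicity method has to match the way in which the tests multiply. Here they multiply because many markers are each compared between groups. Scheffé's procedure answers a different question: for a single marker, it controls the error over every contrast that could be formed among the group means. Running it separately on each marker leaves the error across markers where it was.

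A reader of the results would take the exploratory findings as corrected, because the protocol promises this. If the named method is followed, they may not be.

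The family to be corrected is also unclear, because some listed markers do not appear among the planned measurements.

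**Working it through.** The protocol gives no figure of its own on this point, so there is nothing to reproduce first.

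**Inputs**
- Eleven exploratory items (Data Analysis).
- A per-test level of 0.05. The protocol states it for the primary and secondary hypotheses. Its use for the exploratory tests is an assumption.
- Two groups. The protocol states this for PKC and FMD. Its use for the exploratory outcomes is an assumption.
- Group size. The power section speaks of "comparing the net change between the two ethnic groups of 20 individuals who will change from a traditional Asian diet to an American diet"; the Study Design text and the first power table give 25 per group. Both are run below.
- Four ethnicity-by-diet cells with 50 subjects in all (20 + 5 per ethnic group, power section), for the alternative reading.

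**Step 1: two groups.** The Scheffé critical value for a contrast is √[(k−1)·F(0.95; k−1, N−k)]. With k = 2 it is √F(0.95; 1, N−2), which is t(0.975; N−2) by identity.

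| Groups | df | Scheffé | two-sided t |
|---|---|---|---|
| 20 + 20 | 38 | 2.024 | 2.024 |
| 25 + 25 | 48 | 2.011 | 2.011 |

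The correction is zero, whichever group size applies.

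**Step 2: error across outcomes when each is tested at 0.05.** With m independent outcomes, the chance of at least one false positive is 1 − 0.95^m.

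- m = 8 (without fibrinogen, E-selectin and Fox II): 1 − 0.95^8 = 0.34
- m = 9 (Fox II counted as measured): 1 − 0.95^9 = 0.37
- m = 11 (all named items): 1 − 0.95^11 = 0.43

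The markers are unlikely to be independent. A simulation of eleven equally correlated normal outcomes, 20 v 20, with 20,000 runs for each setting, gives:

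| Correlation | Chance of at least one false positive |
|---|---|
| 0.3 | 0.38 |
| 0.5 | 0.31 |
| 0.8 | 0.19 |

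For comparison, a Bonferroni correction over eleven outcomes would use 0.05/11 = 0.00455 per test, which is a critical |t| of 3.016 at 38 degrees of freedom instead of 2.024.

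**Step 3: four cells.** With k = 4, N = 50 and df = 46, the Scheffé value is √[3·F(0.95; 3, 46)] = 2.90, against t = 2.01. The level for one contrast is then about 0.0057. One pre-chosen contrast on each of eleven independent outcomes gives 1 − (1 − 0.0057)^11 ≈ 0.06. That figure follows from the number of cells and would rise with more outcomes. If all contrasts are in play, each outcome carries 0.05 and the rate over eleven independent outcomes is again 0.43.

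**Step 4: the list against the measurements.** The list runs "lipids, fibrinogen, IL-6, TNF-alpha, E-selectin, Isoprostane, Fox II, leptin, adiponectin, and ghrelin", preceded by anthropometrics. Checked against Details of Measurements, the Study Procedures Flow Sheet and Details of Outcome Measurements:

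- Anthropometrics, lipids, IL-6, TNF-alpha, isoprostane, leptin, adiponectin and ghrelin: measured.
- Fibrinogen and E-selectin: not named in any of the three places.
- Fox II: not named. The unspecified RNA entry among the inflammatory markers might cover it, but the protocol does not say so.

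**The case against.** The strongest objection is that the protocol fixes a two-group comparison only for PKC and FMD. The design has four ethnicity-by-diet cells, and the same section plans a comparison of exposed with unexposed subjects within each ethnicity. A procedure for contrasts suits that setting, where it is clearly stricter than a t-test. This stands in part: it would be too strong to say that Scheffé corrects nothing under any reading. But no four-cell model is stated for these outcomes, and even there the adjustment ignores how many outcomes are tested.

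Second, the sentence that follows promises correction for all exploratory hypotheses, and a statistical analysis plan that is not shown could supply a method. Leaving the method to that plan would be no fault. The difficulty is that the protocol does name one, and the promise that follows puts nothing in its place.

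Third, 0.43 should not be read as the expected error rate. It counts three items without a clearly stated measurement and assumes independence. Eight items give 0.34, and correlation lowers the figure further. In the other direction, lipids and anthropometrics each hold several variables, so the true count of tests is not fixed.

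A reader might also infer that leaving PAI-1, IL-8 and IL-1 off the exploratory list is an error. It is not, because the list is open. Nor does the text say that exploratory p-values will choose the mediators for later studies. It says only that further studies would be designed if change from baseline differs between groups. The study is labelled a pilot, and no confirmatory claim rests on these tests.

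**Conclusion.** The point holds in a limited form. The protocol promises correction across the exploratory hypotheses, and the one method it names does not act across outcomes.

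If the exploratory outcomes follow the two-group comparison used for PKC and FMD, the correction is exactly zero. The chance of at least one false signal is then roughly 0.2 to 0.4, depending on the number of outcomes and their correlation. This assumes that each test is run at 0.05 and that no marker truly differs between the groups. Under a four-cell analysis the rate could be as low as about 0.06 for one pre-chosen contrast per outcome, but only by coincidence of the number of cells.

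Separately, fibrinogen and E-selectin are listed for analysis without any stated measurement, and the position of Fox II is unclear.

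The primary and secondary tests are unaffected. This should be corrected, but it does not threaten the main result.

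**What to change.** Replace Scheffé's procedure with a method that works on p-values across outcomes. Holm controls the chance of any false positive; Benjamini-Hochberg controls the expected share of false positives among those declared. Either can be applied to t-test or Wilcoxon p-values, so it fits the protocol's choice between parametric and rank tests.

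State the family in the same place:
- Keep PKC (primary) and FMD (secondary) outside it.
- Say whether CRP belongs to it. The power section treats CRP beside FMD, but the exploratory list does not name it.
- Say which comparison is made for each exploratory outcome.
- Reconcile the list with Details of Measurements: add the assays for fibrinogen and E-selectin or drop the two markers, and say whether RNA covers Fox II.

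This takes a sentence or two and a corrected list, with no extra subjects or visits. Assay work is needed only if the missing markers are kept. The price is somewhat larger exploratory p-values: with Holm over eight outcomes, the smallest would be compared with 0.05/8 = 0.00625.

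### The only planned look by ethnicity at the randomised diet effect is a pair of low-power within-ethnicity significance tests, with no diet-by-ethnicity contrast

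*Protocol*

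**What the plan says.** The relevant statements are in two sections of the protocol.

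- **Primary test (Data Analysis).** The main hypothesis "is to detect if there is a difference in PKC activity change between Caucasians and Asians with exposure to American diets". It is a two-sample test of PKC change between the ethnic groups. The power section bases it on those who switch diet.
- **Look by ethnicity at diet (Data Analysis).** After a sentence on confounders comes "The potential role of effect-modifiers will also be considered in the interpretation of the data", followed at once by "A preliminary stratified examination will be done to determine if there is a significant difference between exposed and unexposed groups of the same ethnicity".
- **Multiplicity (Data Analysis).** The section says that "correction for multiple comparisons will be applied for all exploratory hypotheses". It does not say whether the within-ethnicity tests count among these.
- **Alpha (Sample size and power calculations).** "An assumption of a one-sided test with an alpha of 0.05 was made". For the comparison with controls: "An appropriate two-sample test will be used for this determination, with the alpha and power given in the proceeding paragraph". No division of alpha between the two ethnicities is mentioned.
- **Group sizes.** The power section has "A total of 25 individuals of each ethnic group will be randomized into either the traditional Asian diet group (n=5) for each period", with the other 20 switching to the American diet, and the table under Study Design agrees. The Study Design text and power Table 2 instead give 10 controls and 25 switchers.

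No contrast of the diet effect between ethnicities is named anywhere.

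**The concern.** Subjects are randomised to diet within each ethnicity. The randomised evidence on whether the diet effect differs by ethnicity is therefore the difference between two differences: Western v continued Asian diet in Asians, against the same in Caucasians. The protocol does not plan that comparison. It plans a significance verdict in each ethnicity separately.

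If one ethnicity is significant and the other is not, the pair will look like an answer to the trial's main question. It is not one. With five or ten controls per ethnicity, such a split is common when the diet effect is identical in both groups. Table 2 adds to the risk, because its stated power of 0.875 for a 5% change would lead a reader to take a non-significant stratum as evidence of no effect.

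**Working it through.** **Inputs (Sample size and power calculations, Tables 1 and 2).** Control PKC is 78.1, SD 5. With a 5% change it is 82.005, SD 5.25 (difference 3.905). With a 10% change it is 85.91, SD 5.5 (difference 7.81). Alpha is 0.05. Sizes per ethnicity are 20 v 5 or 25 v 10.

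**Step 1: reproduce the plan's figures.** Power = Φ(δ / √(s₁²/n₁ + s₂²/n₂) − z).

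- Table 1, 5% row, 25 v 25, one-sided: 3.905 / √(25/25 + 27.5625/25) = 2.693, and Φ(2.693 − 1.645) = 0.8527. This matches the stated 0.8527.
- Table 2, 5% row, 10 v 25, one-sided: 3.905 / √(25/10 + 27.5625/25) = 2.057, and Φ(2.057 − 1.645) = 0.66 (0.54 two-sided). The stated 0.875 is not reproduced.
- No power is stated for 20 v 5.

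**Step 2: power in one ethnicity at 20 v 5, 5% effect.** 3.905 / √(25/5 + 27.5625/20) = 3.905 / 2.526 = 1.546. One-sided power is Φ(1.546 − 1.645) = 0.461, and two-sided power is 0.340. A t test on 23 degrees of freedom with the pooled SD (5.21) gives 0.425 and 0.301.

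**Step 3: chance of split verdicts when the effect is the same in both.** The two ethnicities are independent, so P(exactly one significant) = 2p(1 − p). The maximum is 0.5, at p = 0.5.

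| Size per ethnicity | True effect in both | Split, one-sided (normal, t) | Split, two-sided (normal, t) |
| --- | --- | --- | --- |
| 20 v 5 | 5% | 0.50, 0.49 | 0.45, 0.42 |
| 20 v 5 | 10% | 0.15, 0.22 | 0.23, 0.33 |
| 25 v 10 | 5% | 0.45, 0.47 | 0.50, 0.50 |
| 25 v 10 | 10% | 0.02, 0.03 | 0.04, 0.07 |

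At 20 v 5 the split is about 2% or less for a 15% effect and about zero for 50%. With no effect at all, if each test were run at 0.05, at least one would be significant in 1 − 0.95² = 9.75% of trials.

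**Step 4: sensitivity to the SD.** The endpoint is percent change, whose SD the protocol does not give. Assume SD 5 at both visits and within-person correlation ρ, so that the SD of percent change is about 100·√(2·25·(1 − ρ))/78.1. This is 9.05, 6.40 and 4.05 for ρ = 0, 0.5 and 0.8. At 20 v 5 and a 5% effect, one-sided t-test power is 0.28, 0.45 and 0.77, and the split is 0.41, 0.50 and 0.35. At a 10% effect the split is 0.43, 0.15 and below 0.01.

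**Step 5: the single contrast.** With a common SD of 5.25 and 20 v 5 in each ethnicity, SE = 5.25·√(2·(1/20 + 1/5)) = 3.71 PKC units. The 95% interval is about ±1.96 × 3.71 = ±7.3 units. Two-sided 80% power needs a difference of (1.96 + 0.84) × 3.71 ≈ 10.4 units, or 13.3% of 78.1. With identical diet effects, the contrast tested at a two-sided 0.05 falsely declared a difference in 4.95% of 200,000 simulated trials. At 25 v 10 the SE is 2.78.

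**The case against.** A reader might infer that the protocol will judge effect modification by setting one verdict against the other. The documents do not support that. The ethnic difference is tested directly by the primary two-sample test, and the effect-modifier sentence names no modifier. The power section limits the controls to a subset look at outside influences, and the within-ethnicity examination is called preliminary in a study described as a pilot.

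A reader might also infer that each ethnicity is tested at the full 0.05 with no correction. That is not stated either. The power section carries alpha over to the control comparison, and the multiplicity sentence may or may not include these tests. The 9.75% in the working is therefore conditional.

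The figure of one half is a ceiling, reached only when power per stratum is near 50%. It is not a general rate, and at the expected 50% change the problem disappears. That expectation, however, comes from cardiac cells exposed to lipids, and the protocol itself claims adequate power down to 5%.

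It can also be said that subgroup detail belongs in a statistical analysis plan. That would answer a silent protocol. This one fixes a significance criterion within each ethnicity, and calling it preliminary does not remove it. What stands of the objection is that this is a secondary weakness and leaves the primary test untouched.

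**Conclusion.** The point holds in a limited form and is worth changing. The only planned look by ethnicity at the randomised diet effect is two separate tests with low power at the protocol's smallest planned effect. Identical 5% effects would give split verdicts in about 42-50% of trials at 20 v 5 and 45-50% at 25 v 10, so the conflict over group sizes does not decide the matter. At a 10% effect with 20 v 5 the range is about 15-33%.

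These figures rest on the protocol's cross-sectional PKC standard deviations and on independent ethnic groups. Over an assumed within-person correlation of 0 to 0.8, the one-sided range at 5% and 20 v 5 is about 35-50%. The finding is not that the protocol plans to draw a false conclusion. Its wording leaves room for one and offers no valid control-based alternative.

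**What to change.** Leave the primary test unchanged. Replace the stratified sentence with wording such as:

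> The effect of Western v continued Asian diet on percent change in PKC will be reported within each ethnicity as an estimate with a 95% confidence interval, without a significance verdict. One exploratory diet-by-ethnicity contrast, with its 95% confidence interval, will be the only control-based evidence on whether the diet effect differs by ethnicity.

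This also removes the doubt about whether the multiplicity correction covers the within-ethnicity tests. The cost is a small wording change and one contrast from data already planned. The price is a wide interval, which should be stated in advance, and the loss of any within-ethnicity claim of significance. The group sizes should be reconciled at the same time, because the precision of the contrast depends on them.
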